**Methods:**

We will conduct a real-world pragmatic clinical trial to evaluate the effectiveness of CHM as a supplementary therapy to prevent neutropenia in patients with breast cancer undergoing chemotherapy. Patients will be classified into CHM or non-CHM groups based on whether they received CHM during chemotherapy. Using generalized estimating equations or repeated measures ANOVA, we will assess differences in white blood cell counts, absolute neutrophil counts, immune cells, and programmed cell death protein 1 (PD-1) expression levels between the 2 groups.

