### Study Design

This study is a real-world pragmatic clinical trial conducted at the Hualien Tzu Chi Hospital in Taiwan. Patients with breast cancer scheduled to receive chemotherapy for their cancer treatment will be recruited as per the flowchart shown in Figure 1. Patients willing to receive CHM during chemotherapy are allocated to the CHM group, whereas those in the non-CHM group will not receive CHM.

To evaluate the effectiveness of CHM, the number of WBCs, the ANC, and the use of G-CSF in patients will be measured. The following questionnaires in Taiwanese will be used: (1) the Brief Fatigue Inventory—Taiwanese Version, (2) the World Health Organization Quality of Life-BREF, (3) the National Cancer Institute-Common Terminology Criteria for Adverse Events & Patient Reported Outcomes, and (4) the body constitution questionnaire. In addition, blood samples will be collected and analyzed for immune profiles and programmed cell death protein 1 (PD-1) expression. Generally, visit 1 represents the first collection of questionnaires and blood samples before the first chemotherapy session. Following the chemotherapy regimen, the first 4 rounds of chemotherapy will be performed every 3 weeks with 3 visits (visits 2-4). Subsequently, 12 rounds of chemotherapy will be performed once per week with another 4 visits (visits 5-8, 3 weeks per visit). Patients will be followed up within 1 month of undergoing chemotherapy. Patients in the CHM group will receive complementary CHM treatment after the first chemotherapy session.

The clinical data will be extracted from the medical history system. The questionnaires will be coded and transformed into numerical values (eg, 5=very satisfied or none, 4=satisfied or light, 3=no change or intermediate, 2=unsatisfied or severe, and 1=very unsatisfied or none) to facilitate statistical analysis. Immune profiles will be analyzed using flow cytometry. The data monitoring committee, clinical trial center of Hualien Tzu Chi Hospital, is independent from the funder and competing interests. The SPIRIT (Standard Protocol Items: Recommendation for Interventional Trials) 2013 checklist is provided in Multimedia Appendix 1 [20].

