### Primary Outcome

The primary outcome used in this study is the number of immune cells, including CD4+ and CD8+ T cells (under CD45+ and CD3+ population), CD56+ NK cells (under CD45+ population), CD19+ B cells (under CD45+ population), CD14+ monocytes (under CD45+ population), and CD11c dendritic cells (under CD45+ population), as well as PD-1 expression levels in these cells. For NK cells, the expression of NKG2D will be also confirmed. The analytic panels used are listed in Table 3.

**Table 3 table3:** Antibodies used for flow cytometry analysis^a^.

Cells or conjugate	FITC^b^	PE^c^	APC^d^	APC-Cy7^e^	PE-Cy7^f^
T cells	CD45^g^	CD4	CD8	CD3	PD-1^h^
B and NK^i^ cells	CD45	NKG2D	CD56	CD19	PD-1
Monocytes or DCs^j^	CD45	CD14	CD11c	—^k^	PD-1

^a^CD45 (304006), CD4 (317410), CD8 (301014), CD3 (344818), and CD19 (302218) were purchased from Biolegend. PD-1 (25-9969-42), CD56 (17-0567-42), NKG2D (12-5878-42), CD14 (12-0149-42), and CD11c (17-0114-82) were purchased from eBioscience.

^b^FITC: fluorescein isothiocyanate.

^c^PE: phycoerythrin.

^d^APC: allophycocyanin.

^e^APC-Cy7: allophycocyanin-cyanine 7.

^f^PE-Cy7: phycoerythrin-cyanine 7.

^g^CD: cluster of differentiation.

^h^PD-1: programmed cell death protein 1.

^i^NK: natural killer.

^j^DC: dendritic cell.

^k^Not available.

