### Statistical Analysis

All statistical analyses will be performed using the SPSS software (version 13.0; IBM Corp) or SAS software (version 9.4; SAS Institute Inc). Continuous variables will be reported as mean and SD, whereas categorical variables will be reported as frequencies and percentages. The Shapiro-Wilk test will be used to analyze the normality of baseline characteristics and outcome variables. The Mann-Whitney *U* test will be used to compare nonnormally distributed continuous data, and the 2-tailed *t* test will be used to compare normally distributed continuous data. The chi-square test will be used to compare categorical data between the groups. Both primary and secondary outcomes involve repeated measurement data. The Friedman test and repeated measures ANOVA will be used to compare the differences between every visit in each group in nonparametric and parametric data, respectively. In addition, we will use generalized estimating equations or repeated measures ANOVA to compare the differences between the 2 groups. We will evaluate the risks of each clinical characteristic by the multivariate logistic regression analysis and adjust the age and other factors or characteristics that may have bias in the analysis. We set *P*<.05 as a significant difference. All data will be recorded in a case report form.

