### Strengths and Limitations

The strength of this study lies in its pragmatic trial design conducted in a clinical setting. Compared with randomized controlled trials, this study design has higher generalizability and provides evidence of its effectiveness in daily practice. This study has some limitations that may have affected the results. First, the internal validity was compromised. A pragmatic clinical trial design could achieve greater generalizability of the effectiveness of CHM as a complementary treatment. To improve internal validity, the statistician analyzing the data was blinded to the group assignment and adjusted for all confounding variables during data analysis. Second, there was a lack of important clinical characteristics, such as dietary and exercise habits. Although dietary intake and moderate-intensity aerobic exercise are crucial for patients with cancer during chemotherapy [36], we could not control daily diet and exercise intensity in this real-world clinical trial. In our clinical setting, oncology nurses educate all participants about the importance of healthy dietary intake and exercise habits during chemotherapy. Third, due to financial considerations, the observation time was not long enough to detect the change in the lymphocyte levels after completing chemotherapy, and further long-term and large-scale studies are needed to evaluate the variation in the number of WBCs and the ANC during the recovery phase after chemotherapy.

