### Conclusions

In conclusion, we have proposed an open-label, single-center, pragmatic clinical trial and a real-world study to evaluate the effectiveness and safety of CHMs for treating CIN in patients with breast cancer. Using this study platform, we will analyze the effects of CHM on the regulation of QoL by evaluating the complications of chemotherapy and immune cell profiles. The findings of this study may contribute to developing an effective intervention for chemotherapy-related neutropenia in patients with breast cancer in clinical practice.

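### Groups are self-selected, but the promised confounder adjustment is not attached to the GEE or repeated measures ANOVA that compares the primary outcome

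*Protocol article*

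**What the plan says.** **Allocation.** Study Design states: "Patients willing to receive CHM during chemotherapy are allocated to the CHM group". The abstract's Methods paragraph has: "Patients will be classified into CHM or non-CHM groups based on whether they received CHM during chemotherapy". Under either wording the patient's own choice determines the group. The Conclusions call the study open-label and single-center, and no randomisation is described.

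**Primary outcome.** "The primary outcome used in this study is the number of immune cells", together with PD-1 expression on those cells. The schedule in Table 2 repeats the immune profile across visits, and Study Design places Visit 1 before the first chemotherapy session.

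**Between-group comparison.** Statistical Analysis: "In addition, we will use generalized estimating equations or repeated measures ANOVA to compare the differences between the 2 groups". The abstract names the same two methods. Neither place mentions a covariate or a role for the Visit 1 value.

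**Adjustment.** The next sentence of Statistical Analysis reads: "We will evaluate the risks of each clinical characteristic by the multivariate logistic regression analysis and adjust the age and other factors". It extends this to other characteristics that might cause bias, without listing them. Strengths and Limitations says the blinded statistician "adjusted for all confounding variables during data analysis", and then that "there was a lack of important clinical characteristics, such as dietary and exercise habits".

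**The concern.** Patients who want CHM may differ from those who do not in age, stage, performance status, regimen and starting counts. Some of these can affect circulating immune cells during chemotherapy. With no randomisation, adjustment for measured pre-treatment factors is the main statistical protection, so the model that carries it is a core choice.

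The article names two models. The one that compares the primary outcome is stated without adjustment, and the one stated with adjustment does not analyse that outcome. A team following the text literally could report an unadjusted group difference as an effect of CHM, while the Discussion tells readers that all confounding was handled.

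**Working it through.** **1. The plan's own figure.** Inputs from Sample Size Estimation: standardised effect 0.5, power 0.80, alpha .05, 10% dropout. A two-sided two-sample t test gives n = 63.77, so 64 per group, with power 0.801 at 64. This reproduces the stated figure; a one-sided test would give 51. Recruiting 70 per group and losing 10% leaves 70 × 0.9 = 63 evaluable, with power 0.795. The calculation is for an unadjusted two-group comparison.

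**2. The statements side by side.**

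| Statement | Model | Suits repeated cell numbers? | Covariates named |
|---|---|---|---|
| Between-group comparison (Statistical Analysis, abstract) | GEE or repeated measures ANOVA | Yes | None |
| Adjustment (Statistical Analysis) | Logistic regression | No, it needs a categorical outcome | Age; the rest unspecified |
| Adjustment (Strengths and Limitations) | None named | Cannot be told | 'All', while diet and exercise are lacking |

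No row combines a suitable model with a named adjustment.

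**3. Size if the group main effect is tested unadjusted.** The documents give no confounder strength, so the following values are assumptions.

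- Bias in SD units = imbalance in the factor (SD) × its correlation with the outcome.
 - Moderate: 0.3 × 0.5 = 0.15 SD.
 - Strong: 0.5 × 0.7 = 0.35 SD.
- Standard error of the difference with 63 per group: √(2/63) = 0.178 SD.
- False-positive rate with no true effect, normal test: P(Z > 1.96 − bias/SE) + P(Z < −1.96 − bias/SE).
 - 0.15/0.178 = 0.84, giving 13.4%.
 - 0.35/0.178 = 1.96, giving 50.2%.
- Cross-check with the noncentral t and 64 per group: a bias of 0.2 SD gives 20.2%. A bias of 0.5 SD, equal to the design effect, gives 80.1%.

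These figures treat the comparison as a single contrast with the variance assumed in the sample size calculation.

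**4. Dependence on the term tested.** Suppose a factor shifts the outcome by b at every visit, including Visit 1. The group main effect is then biased by b. The change from Visit 1 is biased by b − b = 0, so a group-by-visit test removes it. A factor that alters the course under chemotherapy, such as a different regimen, would not cancel in this way. Statistical Analysis does not say which term is the test.

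**The case against.** The strongest reply is that the text does promise adjustment. The sentence straight after the comparison commits to adjusting for age and other potentially biasing factors, Strengths and Limitations repeats the promise without restricting it to logistic regression, and GEE accepts covariates. A reader might infer that the authors plan not to adjust the primary comparison at all. The documents do not support that: they are silent on adjustment in that model, and silence is not a decision against it. What stands is that the promise is tied either to an unsuitable model or to none.

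A second reply is that an article may leave the covariate list and model terms to an analysis plan. That is correct, and a missing list is not the point here. The point is the mismatch between statements that the article does make.

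Third, a reader might infer that Visit 1 is analysed as one more outcome measurement, diluting the effect. The article does not say how Visit 1 enters the between-group model, so this cannot be asserted. Likewise, the false-positive rates apply to a main-effect test and assumed confounder strengths. This reply stands and limits the size claim.

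Finally, the article openly says that internal validity was compromised. That is a fair disclosure, but it sits beside the claim to have adjusted for all confounding variables, and the two cannot both be kept.

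**Conclusion.** The point holds in this form: groups are self-selected, the stated comparison of the continuous repeated primary outcome names no confounder or baseline term, and the promised adjustment is not connected to it. The claim about all confounding variables is contradicted by the admitted lack of diet and exercise data.

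The size is conditional. With an unadjusted main-effect test, 63 per group and an assumed bias of 0.15 to 0.35 SD, the false-positive rate is about 13% to 50% instead of 5%. A group-by-visit test would be free of constant baseline differences, but not of factors that change the course under chemotherapy. The documents do not show which case applies, nor how large any imbalance will be. The correction should be made before the analysis, because the text as written permits a confounded primary result.

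**What to change.** **Statistical Analysis**
- Make the primary between-group comparison one covariate-adjusted GEE or mixed model with group, visit and group-by-visit, and the Visit 1 value of the same marker as a covariate.
- Add prespecified pre-treatment confounders available from the records: age, ECOG score and, where recorded, stage and regimen. Direct adjustment or propensity weighting would both serve.
- Name the contrast to be tested, for example the average post-baseline group difference.
- Do not adjust for on-study G-CSF use. Its frequency is a secondary outcome and is recorded at every visit, so it can itself be affected by treatment.
- Keep logistic regression for binary outcomes.

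**Strengths and Limitations**
- Limit the claim to measured confounders, and word conclusions as adjusted associations. A sensitivity analysis for unmeasured confounding is optional.

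**Cost.** Wording and modest programming, with no new visits; Visit 1 is already collected and clinical data are already extracted from the medical history system. Whether stage and regimen are recorded completely has to be checked. Weighting loses some precision: if the effective sample were an assumed 80% to 90% of 63 per group (50.4 to 56.7), power for an effect of 0.5 would be about 70% to 75%, against 79.5% unweighted. A prognostic Visit 1 covariate may recover part of this. Unmeasured confounding remains under any of these models.

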### Sample Size Estimation

The sample size calculation was based on the mean and SD of the amount of CD4+ between control and treatment groups based on the published literature [19]. By setting the effect size as 0.5, the sample size of each group was estimated as 64 to achieve a power of 0.80 at a significance level of .05 using G*Power software (version 3.1; Heinrich-Heine-Universität Düsseldorf). After accounting for an anticipated dropout rate of 10%, the final sample size was determined to be 70 in each group.

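### No deciding term or visit is named for the between-group comparison of CD4+, and an overall group effect over all visits would count a difference present at the pre-treatment Visit 1 as a CHM effect

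*Protocol article*

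**What the plan says.** The Statistical Analysis section of the protocol article sets out three kinds of test for continuous outcomes, all under one 5% threshold:

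- General two-sample tests: "the 2-tailed *t* test will be used to compare normally distributed continuous data", with Mann-Whitney for non-normal data. No visit is named.
- Within-group tests over time, by Friedman or by ANOVA according to normality. Of these the section says that they "will be used to compare the differences between every visit in each group in nonparametric and parametric data, respectively".
- The between-group comparison: "we will use generalized estimating equations or repeated measures ANOVA to compare the differences between the 2 groups". No term, visit or summary over visits is given.

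The Primary Outcome section lists immune cell numbers and PD-1 levels without a time point. Study Design and Table 2 schedule the immune profile at every visit. Study Design and the administration section put Visit 1 before the first chemotherapy session. CHM begins with or after that session, and patients enter the CHM group because they are willing to take it. Sample Size Estimation uses "the mean and SD of the amount of CD4+ between control and treatment groups" and continues: "By setting the effect size as 0.5, the sample size of each group was estimated as 64". It names no visit.

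**The concern.** The issue is the time dimension of a single measure, not how many immune measures there are. An overall group effect and a group-by-visit interaction answer different questions, and only some contrasts isolate what happened after CHM started.

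The plainest reading of a repeated-measures comparison of two groups is the overall group effect. Fitted to all visits, it averages in a measurement that CHM cannot have influenced. Because patients chose their group, the two groups may already differ at that visit. A stable difference of that kind would then be reported as an effect of CHM. The term also loses power when a real effect appears only late in the course.

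With the deciding term left open, the stated 5% error rate and 80% power are tied to no identified test.

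**Working it through.** **Inputs from the protocol.** Two-sided 5% (two-sided is stated for the t test), standardised difference 0.5, power 0.80, 64 evaluable patients per group, Visits 1-8 with Visit 1 as baseline.

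**Assumptions, not in the protocol.** Normal data, complete data, unit variance at each visit, equal correlation r between visits of 0.3, 0.5 or 0.8, no covariate adjustment, and a Visit 1 difference of 0.5 SD.

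**1. The plan's own figure.** For a two-sample t test the noncentrality is 0.5 × √(64/2) = 2.83 on 126 degrees of freedom, which gives power 0.801. With 63 per group it is 0.795. The stated 64 is therefore reproduced exactly as one two-sided two-sample comparison.

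**2. Overall group effect when the groups already differ and CHM does nothing.** With complete data this term is a two-sample t test on each patient's mean over the 8 visits. The variance of that mean is V = (1 + 7r)/8. A constant 0.5 SD difference gives noncentrality 0.5 × √(32/V).

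| r | V | noncentrality | significant |
|---|---|---|---|
| 0.3 | 0.3875 | 4.54 | 99% |
| 0.5 | 0.5625 | 3.77 | 96% |
| 0.8 | 0.825 | 3.11 | 87% |

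In simulation the interaction stays near 5% in the same setting. Halving the assumed Visit 1 difference to 0.25 SD halves the noncentrality (2.27, 1.89, 1.56), and the group term is then significant in about 62%, 46% and 34% of trials.

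**3. Overall group effect when a true 0.5 SD effect exists only at Visits 5-8.** The mean shift over 8 visits is 0.5 × 4/8 = 0.25 SD, so the noncentralities are those just given and power is again about 62%, 46% and 34%. The interaction exceeds 95% in simulation. The choice of term can therefore decide the conclusion.

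**4. False positives when nothing differs (simulation, 64 per group).**

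- Group effect alone or interaction alone: about 5% each.
- Either of the two: about 10% (two independent tests would give 1 − 0.95² = 9.75%).
- Either of the two, or any visit-wise group test: about 16% to 38% across 7 to 9 visits and correlations from 0 to 0.9. With 8 visits, r = 0.5 and tests at Visits 2-8 it is about 25%.

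**5. A contrast referenced to Visit 1.** Take the change from Visit 1 to the mean of Visits 2-8. Its variance is W = 1 + (1 + 6r)/7 − 2r. A sustained effect is 0.5 SD. An effect at Visits 5-8 only averages 0.5 × 4/7 = 0.286 SD.

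| r | W | power, sustained | power, Visits 5-8 only |
|---|---|---|---|
| 0.3 | 0.800 | 88% | 43% |
| 0.5 | 0.571 | 96% | 56% |
| 0.8 | 0.229 | over 99% | 92% |

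A difference that is constant from Visit 1 onward cancels in this contrast, so its false-positive rate in the setting of step 2 is 5%.

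**The case against.** The strongest objection is that this is a condensed article, and that the choice of model term and the handling of baseline usually belong in the analysis plan. That is fair for modelling detail. It does not cover a primary outcome with no time point, or a power statement attached to no visit, when the analysis that is described can be read plainly as an effect that includes the pre-treatment visit.

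Second, the 0.5 SD Visit 1 difference is assumed, and the problem is partly confounding. Strengths and Limitations promises adjustment for all confounding variables. This softens the scenario. But that promise does not name the Visit 1 value and does not take Visit 1 out of the outcome, and the adjustment in Statistical Analysis sits in the sentence on logistic regression.

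Two stronger readings are tempting and are not supported:

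- A reader might infer that the plan carries a false-positive rate of roughly a quarter. That needs visit-wise tests between the groups, and the protocol mentions every visit only for comparisons within each group. It also needs a correlation the protocol does not give. Even the 10% applies only if either model term alone would be claimed as success.
- A reader might infer that 64 per group fits no repeated-measures term. It does fit one: with complete data the group effect is a two-sample t test on patient means.

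A significant interaction beside a non-significant group effect is also not a contradiction, since they test different hypotheses. The within-group tests are not presented as evidence between groups.

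**Conclusion.** The concern holds in this limited form. No deciding term or visit is fixed for CD4+, and the plainest reading of the plan uses an effect that includes a pre-treatment visit in self-selected groups. On that reading, a 0.5 SD difference already present at Visit 1 yields a significant result in about 87% to 99% of trials with no CHM effect. This rests on 64 per group, complete normal data, an assumed equal correlation of 0.3 to 0.8 and no adjustment for the Visit 1 value. A smaller imbalance gives a smaller but still large rate.

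The error rate from leaving the term open is about 10% for one measure if either model term may be claimed. The 16% to 38% range is conditional on visit-wise group tests that the protocol does not state. The sample size of 64 is correct for a single two-sample comparison; what is missing is the link to a named one.

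**What to change.** In Statistical Analysis, name one deciding between-group contrast for CD4+ that treats Visit 1 as baseline and not as outcome, tested two-sided at 5%. One option is the group difference in change from Visit 1 to the mean of Visits 2-8, taken from the GEE as a group-by-period term (Visit 1 versus later visits). State that the group effect including Visit 1, the full interaction, any visit-wise tests and the within-group tests are descriptive and support no claim of a CHM effect. In Sample Size Estimation, tie the power statement to the named contrast.

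This needs no new patients or data. For a sustained 0.5 SD effect the example contrast has 88% power or more. The real cost is power for an effect confined to Visits 5-8: 43% at correlation 0.3 (where the overall group effect would have about 62%), 56% at 0.5 and 92% at 0.8. If a late effect is the one expected, a different baseline-referenced window can be named, provided it is fixed before the data are analysed. The contrast removes a stable Visit 1 difference only; other confounding from self-selection still needs the planned adjustment.
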